### Statistical analysis

We will isolate the effects of antenatal corticosteroid administration practices using a regression discontinuity design. This design exploits the fact that an infant's probability of receiving antenatal corticosteroids changes significantly based on whether its mother presented to hospital before or after

the 34 week gestational age cut-off. The design assumes that infants immediately below the 34-week threshold are exchangeable with those immediately above the threshold except for the probability of receiving antenatal steroids, mimicking random treatment assignment. In the absence of any treatment effect, outcome rates should be smooth across the 34-week threshold, therefore any estimated change in the outcome at 34 weeks can be assumed to be due to antenatal corticosteroid treatment.

We will implement the design using a multivariable quantile regression model estimating the 50th percentile (for our primary outcome of EDI scores), multivariable log-binomial models (for binary outcomes such as developmentally vulnerable, special needs, and lower respiratory tract infection hospitalization in the first two years of life), and pooled logistic regression models (for binary outcomes where children born in different study years have follow-up time such as ADHD and asthma). In the event that our log-binomial models fail to converge, we will use logistic regression and convert odds ratios to risk ratios using postestimation commands.

Our primary model will include delivery admissions between 31+0 and 36+6 weeks. We will weight observations according to their proximity to the cut-off of 34+0 using a triangular kernel, such that observations closest to the discontinuity are assigned greater weight and those furthest from the discontinuity are given less weight. This weighting is particularly important in this cohort as the probability of birth increases with advancing gestational age, so the largest number of observations will occur furthest from the discontinuity (i.e., at 36+6 weeks).

We will use standard regression discontinuity methods to estimate the size of the discontinuity in child health outcomes due to crossing the threshold at 34+0 weeks (Lee & Lemieux 2010). We will estimate the following regression models for individuals in our sample using a 3-week bandwidth around the gestational age threshold:

$$Y_i = \alpha_0 + \alpha_1 T_i + \alpha_2 T_i^*(GA - T) + \alpha_3 (1 - T_i)^*(GA - T) + \delta X_i + e_i \quad (3)$$

where  $Y_i$  is an outcome for child  $i$  and  $T$  is an 0/1 indicator for being below the threshold at 34+0 weeks. We include separate trends for modeling gestational age ( $GA$ ) above ( $\alpha_1 + \alpha_3$ ) and below ( $\alpha_1$ ) the threshold, and a vector for any other demographic or clinical covariates ( $X_i$ ). As is good practice for regression discontinuity designs, we will also evaluate models with squared terms for the underlying association with gestational age in some specifications, with the final specification based on the Akaike Information Criterion (AIC). We will bootstrap 95% confidence intervals.

The coefficient  $T$  estimates the intention-to-treat (ITT) effect of the intervention, reflecting the impact of the guideline in a real-world setting (in which imperfect compliance with corticosteroid administration occurs because of incomplete courses, mis-timed administration, and insufficient time to administer corticosteroids prior to delivery). We will interpret this coefficient as our primary estimate of the effect of antenatal corticosteroids administration practices on each child health outcome. We will estimate a “per protocol” effect of antenatal steroids by dividing the discontinuity in outcomes estimated by our model by the magnitude of the discontinuity in corticosteroid administration at 34 weeks (estimated in a separate model), but will interpret results cautiously because of the known under-documentation of antenatal corticosteroid administration in our Perinatal Database variable. This under-documentation would likely underestimate the magnitude of the discontinuity in corticosteroid administration at 34 weeks, which, in turn, would over-estimate the causal effect of corticosteroid administration on child health outcomes.

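### Equation (3) subtracts the 0/1 indicator T, not the 34+0 cut-off, from gestational age and mislabels its slopes; read literally, its primary coefficient is not the jump at 34+0

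*Protocol*

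**What the plan says.** All of this stands in the Protocol, section Statistical analysis.

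- **Target.** Standard regression discontinuity methods are to "estimate the size of the discontinuity in child health outcomes due to crossing the threshold at 34+0 weeks".
- **Data.** "Our primary model will include delivery admissions between 31+0 and 36+6 weeks", weighted by a triangular kernel around 34+0.
- **Equation (3).** Apart from covariates and error, it has an intercept α0, a term α1·T_i, a slope term α2·T_i·(GA − T) and a slope term α3·(1 − T_i)·(GA − T).
- **Definition of T.** T "is an 0/1 indicator for being below the threshold at 34+0 weeks". No other definition is given, and the cut-off has no symbol of its own.
- **Slopes in words.** "We include separate trends for modeling gestational age" and, for the coefficients, "above ( $\alpha_1 + \alpha_3$ ) and below ( $\alpha_1$ ) the threshold".
- **Effect.** The coefficient on T "estimates the intention-to-treat (ITT) effect of the intervention". The Protocol adds: "We will interpret this coefficient as our primary estimate of the effect of antenatal corticosteroids administration practices on each child health outcome".

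**The concern.** There are two separate faults.

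First, the running variable is not centred on the cut-off. With T equal to 0 or 1, GA − T is simply gestational age less nothing or less one unit. The coefficient on T_i then compares the two lines near a gestational age of zero, far outside the data, and not at 34+0.

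Second, the text and the equation disagree on which coefficient does what. The text makes α1 the slope below the threshold. In the equation α1 multiplies T_i alone, and the following paragraph takes that coefficient as the ITT effect. One symbol is thus both a nuisance slope and the primary estimate.

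This coefficient is the primary estimate for every outcome. The per-protocol estimate divides the modelled discontinuity by the discontinuity in steroid administration, so a misread coefficient would pass into its numerator too. Fixing the estimator before linkage is the purpose of a pre-analysis plan, so the equation should say what will be estimated.

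**Working it through.** The Protocol states no figure on this point, so there is none to reproduce.

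**Inputs from the Protocol.** T = 1 below 34+0 and 0 otherwise; the terms of equation (3); cut-off 34+0 = 34 × 7 = 238 days; window 31+0 to 36+6 = 217 to 258 days; triangular weights; a cohort of about 16,000.

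**Assumed, not in the Protocol.** The slopes of the EDI score on gestational age, the true jump and the residual SD.

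**Step 1: the literal equation (covariates dropped).**
- Below (T = 1): α0 + α1 + α2(GA − 1)
- Above (T = 0): α0 + α3·GA

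**Step 2: the jump at the cut-off, below minus above.**
- Days: jump = α1 + 237·α2 − 238·α3
- Weeks: jump = α1 + 33·α2 − 34·α3

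**Step 3: solve for α1.**
- Days: α1 = jump + α2 + 238(α3 − α2)
- Weeks: α1 = jump + α2 + 34(α3 − α2)

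So α1 is the lower line at GA = 1 minus the upper line at GA = 0, although the data begin at day 217. With equal slopes the second term vanishes but the offset α2 remains. For the log-binomial and pooled logistic models the same algebra holds on the scale of the linear predictor.

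**Step 4: illustration with assumed slopes (points per week).**

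| GA unit | Slope below | Slope above | True jump | Literal α1 |
|---|---|---|---|---|
| weeks | 0.6 | 0.3 | 0 | 0 + 0.6 − 34 × 0.3 = −9.6 |
| weeks | 0.6 | 0.3 | −1 | −1 + 0.6 − 10.2 = −10.6 |
| days | 0.6 | 0.3 | −1 | −1 + 0.6/7 − 238 × 0.3/7 = −11.1 |
| weeks | 0.5 | 0.4 | 0 | 0 + 0.5 − 34 × 0.1 = −2.9 |
| weeks | 0.5 | 0.5 | −1 | −1 + 0.5 + 0 = −0.5 |

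The second and third rows describe the same data and differ only in the unit of GA. A true discontinuity would not depend on that unit.

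**Step 5: check by simulation.** Triangular-kernel weighted least squares, a mean-regression stand-in for the planned median regression, was fitted to 16,000 simulated admissions over the window. Without noise, the literal form returned the table's values and the form centred on 34+0 returned the true jump each time. With residual SD 8, slopes 0.6 and 0.3 and a true jump of −1 (GA in weeks), the literal form gave α1 = −8.11 (SE 6.58) and the centred form −0.97 (SE 0.23). The literal fit had slopes 0.612 and 0.384, and −8.11 + 33 × 0.612 − 34 × 0.384 = −0.97. Both fits therefore describe the same lines and contain the same jump; only the reading of α1 differs.

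**Step 6: the labels, side by side.**

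| Quantity | Text | Equation (3) |
|---|---|---|
| Slope below | α1 | α2 |
| Slope above | α1 + α3 | α3 |
| Effect at threshold | coefficient on T | α1, the coefficient on T_i |

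Reading the unsubscripted T as the cut-off repairs the centring but leaves this table unchanged. The text's labels suit a different parameterisation, with a main effect of GA plus an interaction of GA with side.

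**The case against.** The strongest reply is that the intention is plain. The section names the jump at 34+0 as the target, invokes standard methods, and centres both the bandwidth and the kernel on the threshold. The equation writes the indicator as T_i and subtracts an unsubscripted T. If that T is the cut-off, the equation is the usual one and α1 is exactly the jump. Subtracting a 0/1 variable from gestational age serves no purpose, so an experienced analyst would hardly code it. If someone did, the inflated standard error would be conspicuous. A distinguishing mark on T may also have been lost in the text taken from the PDF, so the typeset equation should be checked.

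Most of this stands, and it makes a notation slip the likeliest explanation. Two things remain. The only definition given for T is the 0/1 indicator, so the charitable reading has to be supplied by the reader. And the slope labels contradict the equation under either reading.

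A reader might go further and infer that the planned analysis is biased by an amount comparable to the 5-point difference in total EDI that the Protocol calls clinically significant. It is true that 0.021 × 238 = 5.0 and 0.05 × 238 = 11.9. But those slope differences per day are assumptions, and the Protocol gives no slopes from which to judge them. The 5-point figure also refers to the total score, whereas the primary outcome is defined as domain scores.

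**Conclusion.** Equation (3) and its slope labels are wrong as written and should be corrected. Under the only definition of T given, the coefficient named as the primary estimate is jump + α2 + 238(α3 − α2) with GA in days, not the discontinuity at 34+0. This result is algebraic and needs no assumption about the data. The mislabelled slopes are a separate inconsistency that does not depend on how T is read.

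The consequence is conditional. The fitted lines and the jump they contain are the same in either form, so a result would be wrong only if the equation or its labels were coded or read literally. The numerical sizes shown rest on assumed slopes and, for the standard errors, on an assumed SD and the full cohort size. They illustrate the mechanism and do not estimate an error in this study. The documents do not support saying that the design, the target or the intended analysis is faulty.

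**What to change.** Define a separate symbol for the cut-off, c = 34+0 weeks (238 days), keep T_i for the indicator, and write:

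Y_i = α0 + α1·T_i + α2·T_i·(GA_i − c) + α3·(1 − T_i)·(GA_i − c) + δX_i + e_i

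Replace the sentence on trends so that α1 is the ITT discontinuity at 34+0 (below minus above), α2 the slope below and α3 the slope above. State that the squared terms to be compared by AIC are also centred on c, so that α1 keeps this meaning in every specification.

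The cost is one equation and one or two sentences. Data, sample, outcomes and design are untouched.

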## **Exposure measurements**

**Gestational age** in days will be calculated using the gestational age algorithm used clinically during the study period. The estimate of gestational age will be based on the last menstrual period if this estimate is similar to the estimate based on early ultrasound ( $\leq 5$  days if the ultrasound was performed  $< 14$  weeks;  $\leq 10$  days if the ultrasound was performed  $< 20$  weeks). If the gestational age estimate based on last menstrual period disagrees with early ultrasound, or no last menstrual period estimate is available, the ultrasound estimate will be used. Day-specific estimates of ultrasound-based gestational age are available in the BC Perinatal Data Registry as of April 1, 2008. Prior to this period, we will calculate day-specific gestational age based on the date of the last menstrual period among women

whose ultrasound-based estimate of gestational age (in weeks) is the same or within 1 week of their estimate based on last menstrual period (in weeks). We will use gestational age in days at the time of maternal admission for the delivery as our unit of analysis, which better approximates timing of antenatal corticosteroid administration compared with gestational age at delivery. We will conduct sensitivity analyses to explore the potential for bias due to exclusion of women with missing day-specific gestational age estimates.

Antenatal corticosteroid administration is available in the BC Perinatal Data Registry as a binary variable indicating the administration of corticosteroids during the delivery admission for the purpose of fetal lung maturation. This can be any type of corticosteroid (e.g., betamethasone or dexamethasone) and does not reflect dosing information. This variable is known to underestimate the true administration rates, as administration during an antenatal admission shortly prior to delivery is not captured (i.e., a patient is admitted, receives antenatal corticosteroids, but is discharged without delivering). We will obtain this variable to confirm the change in the probability of receiving antenatal corticosteroids according to gestational age, but are using the gestational age discontinuity, not the provision of steroids *per se*, as our primary exposure.

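### The 'per protocol' ratio is not tied to a mean or risk difference, so as written it does not estimate the effect of steroids in compliers at 34+0 weeks

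*Protocol*

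**What the plan says.** The Statistical analysis section assigns a model to each type of outcome:

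- **EDI scores (primary):** "We will implement the design using a multivariable quantile regression model estimating the" 50th percentile.
- **Binary outcomes:** "multivariable log-binomial models (for binary outcomes such as developmentally vulnerable, special needs, and lower respiratory tract infection hospitalization" in the first two years of life. If these fail to converge, logistic regression is used and odds ratios are converted to risk ratios. That is the only conversion named.
- **ADHD and asthma:** "pooled logistic regression models (for binary outcomes where children born in different study years" have unequal follow-up).

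The coefficient on the threshold indicator "estimates the intention-to-treat (ITT) effect of the intervention, reflecting the impact of the guideline in a real-world setting", and the protocol makes it the primary estimate for each outcome.

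A second, 'per protocol' effect is formed "by dividing the discontinuity in outcomes estimated by our model by the magnitude of the discontinuity in corticosteroid administration at 34 weeks". The denominator comes from a separate model whose scale is not given. Exposure measurements says that the steroid variable is there to "confirm the change in the probability of receiving antenatal corticosteroids according to gestational age", which points to a difference in probability. The only caution attached to the ratio is under-recording of steroid use.

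Under Sensitivity analyses, the paragraph on women who may have had steroids in a prior admission makes this ratio, in women with no earlier hospitalization in the pregnancy, the primary estimate of the effect of corticosteroids themselves.

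**The concern.** Dividing an outcome jump by a treatment jump works because a mean, or a risk, in a mixed group is a weighted average of its treated and untreated members. The outcome jump is then the complier effect multiplied by the jump in treatment, and division undoes the multiplication. Medians, log risks and log odds are not weighted averages of this kind, so division does not return the complier median effect, risk ratio or odds ratio.

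At stake is the plan's only estimate of what steroids do, as distinct from what the guideline cut-off does. Restricting to women without earlier admissions addresses under-recording but leaves the scale problem in place. The direction of the error also varies between scenarios, so a reader could not correct for it afterwards.

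**Working it through.** The protocol gives no steroid uptake, outcome risk or power figure, so there is no planned figure to reproduce. The check compares the planned ratio with the true complier effect.

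**Inputs from the protocol** (Child health outcomes): total EDI median 41 of 50, 25th percentile 35, and 5 points as the clinically significant difference. The total is used because these percentiles are given for it.

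**Assumptions:** jump in steroid use d = 0.3 to 0.5; no use above the cut-off; same baseline risk in compliers and others.

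**1. Risk ratios.** Let r0 be the risk above the cut-off and RR the ITT risk ratio. The complier risk difference is r0(RR − 1)/d, so the complier RR is 1 + (RR − 1)/d. Dividing the log-binomial coefficient by d gives exp(ln RR / d).

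| ITT RR | d | True complier RR | From the log RR |
|---|---|---|---|
| 1.10 | 0.5 | 1 + 0.10/0.5 = 1.20 | 1.10^(1/0.5) = 1.21 |
| 1.10 | 0.3 | 1 + 0.10/0.3 = 1.33 | 1.10^(1/0.3) = 1.37 |
| 0.80 | 0.5 | 1 − 0.20/0.5 = 0.60 | 0.80^(1/0.5) = 0.64 |
| 0.80 | 0.3 | 1 − 0.20/0.3 = 0.33 | 0.80^(1/0.3) = 0.48 |

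**2. Odds ratios.** Assume an untreated risk of 0.10 and a true OR of 2.25 (risks 0.10 and 0.20). With steroid use of 0.5 below and 0.1 above the cut-off, the risks on the two sides are 0.15 and 0.11. The log OR divided by 0.4 gives 2.44. The risk-difference ratio is (0.15 − 0.11)/0.4 = 0.10, which is the true difference.

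**3. Unequal baseline risk.** Take no use above the cut-off, a true complier RR of 2.0 from a baseline of 0.10, and never-treated risk of 0.05 or 0.20. The log-RR ratio gives 4.21 or 1.69 at d = 0.2, and 2.54 or 1.81 at d = 0.6. The risk-difference ratio stays at the true 0.10 throughout.

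**4. Medians.** A beta distribution with parameters 5.03 and 1.35, multiplied by 50, has median 41 and 25th percentile 35. The score distribution below the cut-off is a mixture with share d treated. Its median is found by root-finding, and the difference from 41 is divided by d.

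| Effect in treated children | True complier median effect | Median ratio, d = 0.3 | Median ratio, d = 0.5 |
|---|---|---|---|
| All lose 5 points | −5.0 | −5.5 | −5.4 |
| 25% lose 20 points | −3.7 | −2.7 | −2.9 |

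The ratio overstates a uniform shift slightly and understates a harm concentrated in a minority. In the second row the mean effect is 0.25 × (−20) = −5.0. That is a different estimand, but it equals the protocol's threshold of clinical significance.

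**The case against.** **The text never says that logs are divided.** It speaks of the discontinuity in outcomes, and equation (3) is additive in the outcome. Risks predicted on each side of 34+0 by the fitted model, then differenced, would fit the wording and be valid. This is fair for the binary outcomes: the protocol leaves the scale open there and does not state a wrong one. But the numerator is tied to what the model estimates, the named models have other scales, and the only conversion goes from odds ratio to risk ratio. For the EDI there is little room: the model's discontinuity is a difference in medians.

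**The errors are small in plausible cases.** This stands. Modest effects with similar baseline risk give errors of a few hundredths in the RR, and with no effect in anyone the ratio is zero on the difference and log scales. Nothing in the protocol shows that compliers differ in baseline risk, so step 3 is a possibility only.

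**The ITT coefficient is the primary estimate.** This also stands, and it limits the severity. It does not remove the point, because the ratio is later named the primary estimate of the steroid effect.

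**Stronger readings.** A reader might infer that the ratio is biased for every outcome whatever the truth, that the primary analysis is undermined, or that a protective effect would turn harmful because the RR itself is divided by d. The documents support none of these: the error needs a non-null effect, the ITT models do not use the ratio, and dividing the RR itself is suggested nowhere.

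**Conclusion.** The concern holds as a should-fix. Taken with the models it names, the stated formula does not estimate the complier effect at 34+0 weeks when steroids have an effect. The error runs from negligible (ITT RR 1.10) to material: a complier RR of 0.33 reported as 0.48, or a complier median loss of 3.7 EDI points reported as 2.7 to 2.9. These sizes depend on the assumed jump, one-sided uptake, equal baseline risk and fitted EDI distribution; that the ratio needs an additive scale does not.

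A reader might also take the additive ratio as the effect in all treated children. It is the effect in compliers at the cut-off, given that crossing the threshold acts only through steroids and moves nobody's treatment the opposite way. The label 'per protocol' does not describe that quantity.

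**What to change.** Keep the ITT models as they are. For the steroid effect, state the following:

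- Compute a fuzzy regression discontinuity ratio on the additive scale: mean difference for the EDI, risk difference for binary outcomes. Use a linear model, or risks predicted on each side of 34+0 by the fitted models.
- Express the steroid jump as a difference in probability. Use the same children, kernel, window and covariates in both stages. For the EDI this means fitting the steroid model in the children who contribute EDI scores, since the waves cover only about a third of children in a given year.
- Bootstrap both stages together.
- For ADHD and asthma, use the difference in cumulative risk at a stated age with adequate follow-up, predicted from the pooled logistic model. Later follow-up, up to about 18 years for the earliest births, then need not be discarded.
- Call the result the complier effect at 34+0 weeks. If a median effect is wanted, use a complier quantile estimator.

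The cost is plan wording and a few extra models, with no new data. There are two downsides. The steroid effect will be on a different scale from the ITT risk ratios, odds ratios and medians. A mean EDI effect will also depend more than a median does on the lowest observed score assigned to children who died.

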## Overview of research plan

We will estimate the effect of antenatal corticosteroid use on child neurodevelopmental outcomes using a novel quasi-experimental design that exploits the clinical cut-off of antenatal corticosteroids administration at 34 weeks. We will link abstracted obstetrical and neonatal chart records from approximately 16,000 preterm births delivered from 2000 to 2013 contained in the British Columbia (BC) Perinatal Data Registry with longer-term child health information contained in BC population-based administrative databases and kindergarten testing data. We will isolate the difference in test scores and adverse child health outcomes occurring at 34 weeks using a regression discontinuity design, while accounting for the general decrease in adverse outcomes associated with advancing gestational age. The study was approved by the Research Ethics Board of the BC Children's & Women's Hospital/University of British Columbia (H18-00620).

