## **Data**

Our study cohort will be created through a linkage of British Columbia's comprehensive population-based databases of detailed obstetrical medical records, medication prescriptions, physician billing, hospital discharge records, vital statistics, and kindergarten child development assessments. The linkage will be performed by PopData BC, a multi-university organization that facilitates the use of the province's databases for research purposes. Maternal and infant personal health numbers and dates of birth will be used as unique identifiers. The linked data are accessed in an anonymized format on a secure server to ensure data confidentiality and security. Follow-up data up to March 31, 2018 will be included, ensuring a minimum of 5 years follow-up for all children.

**BC Perinatal Data Registry:** The BC Perinatal Data Registry contains abstracted obstetrical and neonatal medical records for >99% of deliveries in the province since April 1, 2000. Data quality are maintained through the use of provincially-standardized medical record forms, standardized training of abstractors (certified following a 2-year training program), and regular data checks for plausibility and missing values. Validation studies have established the accuracy and completeness of the database.

**Early childhood development data:** British Columbia has been conducting standardized assessments of child development at kindergarten age since 2001 using the Early Development Instrument, a questionnaire used across Canada and internationally. Data are collected in 3-year waves, so are only available for approximately one-third of children in the province a given year.

**Hospital Discharge Abstract Database:** The BC Hospital Discharge Abstract database contains International Classification of Disease (ICD) codes summarizing the diagnoses and procedures for all discharges, transfers and deaths of inpatients in acute care hospitals in British Columbia. We will only use the first 16 diagnostic coding spots, to ensure that the number of diagnostic coding spots is consistent throughout the study period (a greater number of spots are available in more recent years).

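### The 'per protocol' ratio does not tie the gestational-age form of the outcome model to that of the steroid model, so if AIC picks different orders the ratio can be biased in either direction

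*Protocol*

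**What the plan says.** All of the following is in the Protocol.

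- **Ratio.** Statistical analysis divides the modelled outcome jump "by the magnitude of the discontinuity in corticosteroid administration at 34 weeks (estimated in a separate model"). The order, window, kernel, covariates and children of that separate model are not stated.
- **Choice of form.** Squared gestational-age terms will be tried, "with the final specification based on the Akaike Information Criterion (AIC"). The sentence follows the outcome equation. No rule links the order chosen there to the order of the steroid model.
- **Outcome fit.** It is made "using a 3-week bandwidth around the gestational age threshold". The plan is to "weight observations according to their proximity to the cut-off of 34+0 using a triangular kernel".
- **Outcome scale.** The primary outcome uses a "multivariable quantile regression model estimating the 50"th percentile. Binary outcomes use log-binomial or pooled logistic models.
- **Data.** The cohort has "approximately 16,000 preterm births delivered from 2000 to 2013". For the Early Development Instrument (EDI), the Data section says: "Data are collected in 3-year waves, so are only available for approximately one-third of children in the province a given year".
- **Status.** The intention-to-treat coefficient is the primary estimate. The ratio is to be read with caution because steroid use is under-recorded. The sensitivity analysis that excludes women with a prior admission makes that subgroup the main setting for the ratio.

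**The concern.** A ratio of two regression-discontinuity jumps is protected against a misfitted uptake curve only if both jumps carry the same misfit. Selecting each form separately removes that protection.

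The two selections could easily disagree. Steroid use is a field in a registry that covers nearly all deliveries, and a bend in it is easy for AIC to detect. EDI scores are noisy and exist for about one-third of children, so AIC will more often stay with the linear form there.

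This ratio is the plan's way of expressing the effect of receiving steroids rather than of the guideline. A mismatch would shift it for a purely technical reason. The Protocol's stated caution about under-recording pushes in one direction only, towards over-estimation. A mismatch can push either way and is not mentioned.

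**Working it through.** The Protocol gives no uptake curve, uptake jump or 'per protocol' figure, so there is nothing to reproduce. The check asks how large the effect of a mismatch could be.

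**Inputs from the Protocol**
- 31+0 to 36+6 weeks gives 21 days on each side of 34+0, consistent with the 3-week bandwidth; triangular kernel.
- About 16,000 births; one-third with EDI gives 16,000 / 3 ≈ 5,333.
- EDI SD from the quoted 50th and 25th percentiles, assuming normality: (41 − 35) / 0.6745 = 8.9.
- Effect of −5, the Protocol's clinically significant difference, used here as the per-treated effect; 0 was also run.

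**Assumption.** Three uptake curves: piecewise linear (true jump 0.35), mildly curved (0.27) and strongly curved (0.10).

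**Step 1: why matching works.** Write Y = g(GA) + b·S + error, with g smooth and S steroid receipt. Let J_p(·) be the jump from a kernel-weighted least-squares fit of order p. J_p is linear in the data, so J_p(Y) = J_p(g) + b·J_p(S). If g is linear in gestational age, J_p(g) = 0, and the ratio is

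R(p, q) = J_p(Y) / J_q(S) = b · J_p(S) / J_q(S).

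With p = q this equals b, however badly J_p(S) misses the true uptake jump. With p ≠ q it does not.

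**Step 2: large-sample size of the mismatch (b = −5)**

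| Uptake curve | J(S) linear | J(S) quadratic | Linear / quadratic | Quadratic / linear | Matched |
|---|---|---|---|---|---|
| Piecewise linear | 0.35 | 0.35 | 1.00 | 1.00 | 1.00 |
| Mild | 0.357 | 0.297 | 1.20 | 0.83 | 1.00 |
| Strong | 0.367 | 0.245 | 1.50 | 0.67 | 1.00 |

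Example, mild curve: 0.357 / 0.297 = 1.20, so the ratio tends to about −6.0 instead of −5. With a curved background trend g, matched linear gives 1.02 and matched quadratic 1.00. Other assumed curves gave 1.13 to 1.42 for linear over quadratic and 0.71 to 0.83 for the reverse.

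**Step 3: separate AIC selection.** 600 replicates per scenario, weighted least squares with Gaussian AIC. This is a mean model, not the planned median regression.
- Effect −5, curved uptake: the orders differed in 73–76% of runs (mild) and 54% (strong). Median ratios were −5.7 to −5.9 (mild) and −6.2 to −6.3 (strong). The extremes are 5.72 / 5 = 1.14 and 6.28 / 5 = 1.26 times the truth.
- Effect −5, piecewise-linear uptake: median −5.02 to −5.03.
- Effect 0, curved uptake: medians −0.11 to −0.15, no material bias.

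**Step 4: different children.** Linear order in both fits, effect −5, mild curve:

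| Denominator from | Median | SD |
|---|---|---|
| Same EDI children | −5.03 | 1.83 |
| All births | −5.11 | 1.86 |
| Disjoint births | −5.13 | 1.91 |

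**Step 5: spread (SD), mild curve, effect −5.** Matched linear 1.83; linear over quadratic 2.35; separate AIC 2.91 to 2.96; matched quadratic 3.32.

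**Step 6: outcome scale.** Step 1 needs a linear mean model.
- Median regression, matched orders (n = 120,000, symmetric errors), with the effect confined to the lower half of children: median ratios from −1.10 to +1.22, against mean ratios from −4.19 to −5.47.
- Risk ratio: with a true treated risk ratio of 1.5, a risk difference of 0.05 and an uptake jump of 0.27, the intention-to-treat risk ratio is 1.124. Then 1.124 / 0.27 = 4.16, which is not a per-treated effect. The risk difference divided by 0.27 returns 0.05.

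**The case against.** The case for leaving the text alone has several parts.

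- **A separate model is not a separate specification.** Any such ratio needs two regressions, the AIC sentence is attached to the outcome equation, and first-stage detail is often left to a later analysis plan. It is true that the Protocol does not say the orders will differ. But this document calls itself the pre-analysis plan, defines the ratio and leaves the form to a data-driven rule without linking the two fits.
- **The bias is conditional.** It needs curved uptake, a non-zero effect and differing orders, and the Protocol shows no uptake curve. This stands in full.
- **The ratio is not primary.** It is already flagged for cautious reading. This stands, although the flag concerns under-recording only.
- **Cancellation is not exact for the planned models.** This also stands. Median, log-binomial and pooled logistic fits are not linear mean models, so matching the order alone is not a complete repair.

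A reader might also infer two stronger points. The first is that the two jumps come from different children and that this biases the ratio. The Protocol never says so; it is a deduction from data availability, and the restriction to women without a prior admission suggests a common cohort. Different children did almost nothing in Step 4, provided that the EDI third has the same uptake curve as the rest. The second is that the planned ratio is simply noisier. It is noisier than a common linear form, but in Step 5 both separate selection and a mismatched pair were less variable than a matched quadratic.

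**Conclusion.** The concern holds in a conditional form. The Protocol leaves the order of the two fits untied, and if the orders differ, curvature error in uptake does not cancel. The 'per protocol' ratio can then be about 0.7 to 0.8 or 1.2 to 1.5 times the truth. These figures rest on assumed uptake curves, a constant effect and a mean-scale outcome model. They show the possible scale and do not predict the result in these data.

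The documents do not support saying that the ratio is biased as a matter of fact. The primary intention-to-treat estimate and its interpretation are unaffected. The change is worth making because a matched specification is a better method at almost no cost, but it concerns a non-primary estimate.

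**What to change.** For the 'per protocol' ratio only:

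- Estimate both jumps with one pre-specified polynomial order, the same window, the same triangular kernel and the same covariates, preferably in the same children.
- Use a mean scale for EDI scores and a risk-difference scale for binary outcomes. The ratio is then equivalent to kernel-weighted two-stage least squares.
- Bootstrap numerator and denominator jointly, resampling children once and recomputing both.
- Report the other order, applied to both jumps, as a sensitivity analysis.
- Apply the same rule in the subgroup without a prior admission.

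The cost is plan wording and no new data. There are two small downsides. For EDI outcomes the steroid jump would come from about one-third of births, which hardly changed the spread of the ratio (1.83 with the EDI children, 1.86 with all births). The ratio would also sit on a different scale from the median or risk-ratio intention-to-treat model, so the report should say so.
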